| Blood draw Volume/vacutainer type                                                                                                                                                                                                                                                                                                                                                                                                                                                                                                                              |          |         |         |             |             |         |          |          |          |          |          |                                  |                  |                                       |                       |                       |               |
| EDTA 4ml                                                                                                                                                                                                                                                                                                                                                                                                                                                                                                                                                       | 0        | 0       | 1       | 0           | 0           | 0       | 1        | 0        | 0        | 0        | 1        | 0                                | 0                | 0                                     | 0                     | 0                     | 0             |
| EDTA 9ml                                                                                                                                                                                                                                                                                                                                                                                                                                                                                                                                                       | 3        | 1       | 1       | 0           | 0           | 1       | 1        | 1        | 1        | 1        | 1        | 1                                | 1                | 1                                     | 1                     | 1                     | 1             |
| DBS                                                                                                                                                                                                                                                                                                                                                                                                                                                                                                                                                            | 1        | 1       | 1       | 0           | 0           | 1       | 1        | 1        | 1        | 1        | 1        | 1                                | 1                | 1                                     | 1                     | 1                     | 1             |
| SST 4ml                                                                                                                                                                                                                                                                                                                                                                                                                                                                                                                                                        | 1        | 1       | 1       | 0           | 0           | 0       | 1        | 0        | 0        | 0        | 1        | 1                                | 1                | 1                                     | 1                     | 0                     | 0             |
| Total blood (mls)                                                                                                                                                                                                                                                                                                                                                                                                                                                                                                                                              | 31       | 13      | 17      | 0           | 0           | 9       | 17       | 9        | 9        | 9        | 17       | 13                               | 13               | 13                                    | 13                    | 9                     | 9             |
| Legend: IA : Intervention arm, CA : Control arm. CD4 : CD4+ T-lymphocyte count. DBS : Dried blood spot. DL- : subtherapeutic drug level. DL+ : therapeutic drug level. EDTA : Ethylenediaminetetraacetic acid-containing vacutainer tube. FBC : Full blood count. PE : Physical exam. QoL : Quality of life. SES : Social-economic status. SST : Sodium-separating vacutainer tube. TDM : Therapeutic drug monitoring. VL : Viral load determination. |          |         |         |             |             |         |          |          |          |          |          |                                  |                  |                                       |                       |                       |               |

## 6 OUTCOMES AND ANALYSIS OF RESULTS

### 6.1 Virological and clinical effects of intensified monitoring

Virological outcomes will be differences between arms in (1) the number of drug resistance mutations present, (2) the selection of specific resistance mutations associated with multi-drug resistance (presence of the K65R mutation, or the presence of >1 NNRTI mutation) and (3) consequential loss of therapeutic options. Furthermore, (4) the rate of virological failure in the absence of drug resistance in both arms, unnecessary treatment switches averted in the intervention arm and unnecessary therapy switches made in the control arm will be assessed. An averted case of unnecessary switching will be defined as two sequential elevated VL results in the intervention arm without presence of resistance mutations. Assessment of unnecessary switching in the control arm can be ascertained by retrospective genotypic resistance testing.

Additional virological outcomes will be (5) the time on a failing regimen, defined as the time during which viremia > 1000 copies/mL is maintained after the first instance of a viral load >1000 copies/ml (6) The loss of second line therapeutic options over time in the presence of a failing regimen. Comparison of the extent of drug resistance between both groups will allow for assessment of the clinical consequences of resistance development in both arms. (7) The influence of genotypic resistance testing on the choice for a second line regimen. Genotypic resistance testing results enable the physician to make an informed decision with regard to a follow-up regimen to the first-line regimen. By comparing the chosen regimens in the intervention and control groups, the effect of the availability of genotypic resistance data on clinical decision-making will be compared. These outcomes can be compared between both arms as VL and CD4 measurements will be performed retrospectively in the control group, resulting in an equal frequency of measurements between both arms.

Clinical outcomes will be decrease in CD4 count during failure, QoL as measured using a validated QoL questionnaire, and recorded events of patient morbidity and mortality that can be related to immunological failure.

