## 2.2 Rationale

ART is being rolled out to millions of patients in LMIC. While treatment programmes in LMIC are generally effective, rates of therapy failure, accumulation of drug resistance, unnecessary switching to second-line regimens and (possibly) residual transmission are relatively high. Viral load (VL) monitoring is being implemented in many countries in an effort to improve treatment programme outcomes. However, the optimal cost-efficient frequency of VL monitoring is currently unknown, and a growing body of evidence suggests that significant individual and population health gains can be achieved by expanding viral load monitoring to genotypic drug resistance testing and drug level monitoring (DLM). Conventional tools for resistance testing and DLM are generally not implemented in LMIC due to financial and infrastructural constraints. In pilot projects we have performed field studies using novel low cost solutions for resistance testing and DLM which can be implemented on the individual patient level in LMIC.

Meanwhile, price reductions of VL monitoring have added to the affordability of intensified monitoring strategies in LMIC. These recent developments result in a unique opportunity to assess the added value of intensified VL monitoring in combination with drug resistance testing, DLM, and intensified adherence counseling tailored to DLM results in LMIC.

We have developed a novel low-cost strategy for HIV treatment monitoring that enables early detection of therapy failure, drug resistance and non-adherence, while requiring minimal on-site laboratory capacity and being tailored for implementation in settings with monthly medication collection visits. The strategy consists of intensified VL monitoring every three months. In case of a viral rebound >1000 copies/ml, this will be followed up by repeat VL measurement combined with affordable on-site and real time DLM assay targeting NNRTIs. In case NNRTI concentrations are not detected in plasma tailored intensified adherence counselling is performed. In case NNRTI concentrations are detected, this will be combined with off-site DBS-based genotypic drug resistance testing. Switching to a second line regimen will only be performed if drug resistance is detected.

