## 3 OBJECTIVES

### 3.1 Primary objective – Virological effects of intensified monitoring

To assess the effect of the intensified monitoring strategy versus standard of care monitoring on (1) development and accumulation of resistance mutations and consequential loss of therapeutic options, (2) prevention of unnecessary treatment switches and (3) resuppression rates after intensified counselling.

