#### 5.1.2 Control arm follow-up – standard of care HIV treatment monitoring

300 patients randomly assigned to this arm will be monitored in full concordance with current South African NDoH guidelines in use at the study site. Viral load measurements will be performed at month 12 and 24 after start of ART (for newly initiated patients) or at month 12 and 24 after the last VL measurement (patients already on ART). If a VL >1000 copies/ml is detected, the patient is called back for counselling for therapy adherence and repeat VL measurement, 2 months after the initial VL measurement. If the repeat VL measurement is >1000 copies/ml after adherence counselling, this is taken to be indicative of therapy failure due to development of drug resistance and a switch to second line therapy is made, together with intensified adherence counselling, without verifying the cause of virological failure by

performing DLM or drug resistance testing. If VL drops to <1000 copies/ml after adherence counselling, the first line treatment is maintained. For a full overview of study visits and clinical algorithms in the control arm, see Figure 1: ITREMA study flowchart.

Sample collection in the control arm consists of storage of EDTA-derived plasma and a DBS at study baseline and at the subsequent study visits at month 3, 6, 9, 12, 15, 18, 21 and 24 of ART, as well as during any additional study follow-up visits in case of a VL >1000 copies/ml. Blood draws at baseline, month 3, 6, 12 and 24 after start of ART, and in case of follow-up after a VL >1000 copies/ml coincide with blood draws performed as part of standard of care. The following measurements will be performed on stored samples:

- An additional CD4 measurement at study month 6, in order to assess eligibility for randomisation and rate of CD4-count recovery.
- Retrospective VL testing on stored EDTA-derived plasma in case of clinical therapy failure, in order to retrospectively examine the duration of viremia.
- Retrospective drug resistance testing on stored DBS in case of clinical therapy failure to examine the accumulation of resistance mutations over time.
- Screening for transmitted drug resistance by drug resistance testing on stored DBS obtained as at baseline, prior to start of ART.

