#### 5.2.4 Follow-up of elevated viral load measurement

##### 5.2.4.1 Intervention arm

In case of a VL >1000 copies/ml of a patient in the intervention arm, feedback of this result will be given by the clinical site laboratory after 2-5 working days). The patient will be notified to report back to the research clinician or nurse at his/her next monthly routine clinical visit for medication collection (day 28 after study visit). At this visit repeat viral load testing, DLM and collection of plasma and DBS is performed. If DLM indicates no detectable drug level (see “5.2.5 Drug Level Monitoring”), the patient is informed of this result, and intensified adherence counselling is performed. If DLM does not indicate non-adherence, standard of care adherence counselling will be performed. The result of the second VL will be available after 2-5 working days (day 31-33 after study visit). In case of a second VL >1000 copies/mL and a detectable drug level at DLM, the DBS will be sent to the WHO reference laboratory for drug resistance testing and patients will be notified again to report back to the research clinician or nurse at his/her next monthly routine clinical visit (day 56 after study visit) for genotype guided switch to second-line therapy or for genotype guided continuation of treatment combined with counselling in case no relevant resistance is detected. In case DLM detected no drug level, the DBS is not sent and genotyping not performed. The patient will not be called back and not be switched to second-line therapy prior to the next study visit. In case an elevated VL is again detected at the subsequent study visit (day 84 after previous study visit), a DBS is sent directly for drug resistance testing and genotype guided therapy switch or continuation is performed. In case of continuation, the three monthly monitoring frequency is maintained. In case of switch, a VL will be performed six months after the switch to evaluate initial therapy success. Three monthly study visits will be continued in an observational manner, at which storage of DBS and plasma is performed.

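### The direction, though not the size, of the 'unnecessary switch' comparison is fixed by the two switch rules, its two counts are not comparable, and the converse error has no outcome of its own

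*Protocol*

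**What the plan says.** Protocol section 3.1 lists "prevention of unnecessary treatment switches" as the second of three parts of the primary objective. Section 6.1 turns it into a pair of counts: "unnecessary treatment switches averted in the intervention arm and unnecessary therapy switches made in the control arm will be assessed". The intervention-arm count is defined: "An averted case of unnecessary switching will be defined as two sequential elevated VL results in the intervention arm without presence of resistance mutations". For the other arm, "Assessment of unnecessary switching in the control arm can be ascertained by retrospective genotypic resistance testing".

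The switch rules are:

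- **Intervention arm (section 2.2):** "Switching to a second line regimen will only be performed if drug resistance is detected".
- **Control arm (section 5.1.2):** when the repeat VL is again >1000, "this is taken to be indicative of therapy failure due to development of drug resistance and a switch to second line therapy is made", without drug level monitoring (DLM) or resistance testing.

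Section 5.2.4.1 adds, for an intervention patient at the call-back visit: "In case DLM detected no drug level, the DBS is not sent and genotyping not performed". First-line is then kept until the next study visit, whatever the repeat VL shows. If VL is >1000 again at that visit, genotyping follows regardless of DLM (sections 5.1.3 and 5.2.4.1).

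**The concern.** The genotype that labels a switch unnecessary is also the gate to switching, but in one arm only. A between-arm difference in unnecessary switches would therefore appear even if the strategy changed nothing about viraemia or resistance. The pair of counts does not repair this, because 'averted' and 'made' come from different numbers of tests at different times.

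A decision rule can err in two ways: switching without resistance, or keeping first-line with resistance. Sections 1 and 6.1 name an outcome for the first only, which is the one the intervention rule excludes. At stake is a fair reading of one part of the primary objective. The avoided switches also enter the cost-effectiveness work in section 6.3 as savings.

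**Working it through.** **1. The two rules side by side, after two sequential VLs >1000**

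| | Switched, no resistance | Kept on first-line, resistance present |
|---|---|---|
| Intervention | 0 by rule (2.2) | possible when no drug level is detected (5.2.4.1) |
| Control | every confirmed failure without resistance (5.1.2) | 0 by rule (5.1.2) |

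Only the first column has an outcome in section 6.1.

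**2. Are 'averted' and 'made' comparable?**

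- *Number of tests.* The intervention arm has six scheduled VLs (months 9, 12, 15, 18, 21, 24) and the control arm two (months 12, 24). Section 2.1 itself says that more frequent VL testing may detect more failure without resistance.
- *Timing of the repeat.* In the intervention arm it is drawn 4 weeks later, at the same visit as any intensified counselling. In the control arm it is drawn at 2 months, and section 5.1.2 describes it as following counselling (5.2.4.2 puts both at the two-month visit).
- *Consequence.* 'Averted' can include episodes that annual testing would never have seen, or that would have resolved by 2 months. Those would not have led to a switch under standard care.

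**3. Can 'averted' be determined?** It requires absence of mutations. When no drug level is found, the DBS is not genotyped at the repeat VL. If VL is below 1000 at the next visit, the trigger for later genotyping is not met. The sampling list in section 5.1.3 plans retrospective genotyping only for clinical therapy failure, a term not defined for such a patient. After a month-24 VL >1000 no later three-monthly visit is scheduled.

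**4. How long does the converse error last?** With a detectable level, the genotype-guided decision is due at day 56. Without one, the DBS is sent at day 84 at the earliest, so a resistant patient waits at least 84 - 56 = 28 days longer. If the result again takes one 28-day visit (assumption), the wait is 56 days. Section 2.2 expects resistance risk in this group to be lower, not absent.

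**5. Size when the strategy has no effect on viraemia or resistance**

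The protocol gives no expected count or power for this outcome, so there is no figure to reproduce. Inputs:

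- 300 per arm (5.1.2, 5.1.3).
- Loss of 10% per year (6.7.3), or 15% over 18 months: 300 x 0.85 = 255.
- Cumulative failure f = 20% at 18 months (6.7.3), taken here as confirmed failure; 10% and 15% are shown as lower assumptions.
- Share of failures without resistance r = 13-35% (2.1).

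The control count is Binomial(255, f x r) and the intervention count is 0. At f = 20% there are 255 x 0.20 = 51 failures, of which 51 x 0.13 = 6.6 to 51 x 0.35 = 17.9 are without resistance.

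Thresholds at 255 per arm:

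- Uncorrected chi-square (section 6.7.2 names the test without mentioning a correction): 4 v 0 gives 510 x 16 / (4 x 506) = 4.03, p<0.05.
- Fisher's exact test: 5 v 0 gives p = 0.061 and 6 v 0 gives p = 0.030.

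| f | r | Expected control count | P(count = 0) | P(count >= 4), chi-square | P(count >= 6), Fisher |
|---|---|---|---|---|---|
| 20% | 13% | 6.6 | 0.001 | 0.90 | 0.65 |
| 20% | 35% | 17.9 | <0.001 | >0.99 | >0.99 |
| 15% | 13% | 5.0 | 0.007 | 0.73 | 0.38 |
| 15% | 35% | 13.4 | <0.001 | >0.99 | 0.99 |
| 10% | 13% | 3.3 | 0.036 | 0.42 | 0.12 |
| 10% | 35% | 8.9 | <0.001 | 0.98 | 0.88 |

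The sign is practically certain in every row. The size varies more than fivefold.

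**The case against.** **Section 6.1 also lists failure without resistance in both arms.** True: that two-arm measure stands directly before the averted/made pair, and the protocol nowhere specifies a test of switches made against zero. The test above is an illustration of what a comparison of unnecessary switches would give. The pair is still the outcome that answers part (2) of the primary objective.

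**Retrospective VLs equalise the arms.** Section 6.1 says so. But section 5.1.2 limits retrospective VL testing to clinical therapy failure, and a VL measured later triggers no call-back or switch decision. Equal measurement would not make the two counts alike.

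**The result is still a result.** This stands. A reader might infer that the comparison is settled entirely by the rules. It is not: the control count depends on failure and resistance rates, and whether it reaches significance at the low end depends on the test.

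**The converse error is not ignored.** This stands in part. A reader might infer that it is never counted. Its consequences can enter outcomes (1)-(3), (5) and (6) of section 6.1, and persistent viraemia leads to genotyping at the next visit. The capture is indirect: time on a failing regimen, for example, is not split by resistance.

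**Successful counselling is penalised.** A reader might infer that intensified counselling lowers the 'averted' count by resuppressing patients before the second VL. The documents do not support this, because DLM-triggered counselling takes place at the visit where that VL is drawn.

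**A two-error outcome is also fixed by rule.** Correct: each error is zero by rule in one arm, and a switch to second-line is not equivalent to a delay of weeks. This argues against an unweighted sum, not against showing both errors.

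**The economic model can still go against the strategy.** Agreed. Section 6.3 sets added costs against savings and includes sensitivity analyses.

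**Conclusion.** The concern holds in a limited form. The direction of the unnecessary-switch comparison follows from the switch rules; its size does not. The averted/made pair does not measure the same thing in the two arms, 'averted' cannot be verified for every patient it is meant to cover, and the converse error has no outcome of its own.

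At the protocol's 20% failure and 13-35% without resistance, a strategy with no effect on viraemia or resistance would show about 7-18 control events against 0, with p<0.05 in 0.90 to >0.99 of trials by uncorrected chi-square and 0.65 to >0.99 by Fisher's exact test. These figures assume 255 retained per arm, no deviations from the switch rules, and that the 20% applies to confirmed failure; at 10% or 15% failure with 13% without resistance the chances fall well below this. The documents give no basis for the number of resistant patients kept on first-line.

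This should be changed, because the protocol itself fixes the asymmetric definition. It does not undermine the other primary outcomes.

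**What to change.** In section 6.1 and the Summary, replace the averted/made pair with two outcomes, reported separately per randomised patient in both arms with 95% confidence intervals, after two sequential VLs >1000:

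- (a) switched with no resistance;
- (b) kept on first-line with resistance.

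Classify each by genotype of the DBS stored at the repeat VL. Where this genotype was not already obtained, do it retrospectively and for analysis only, with care unchanged.

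State that (a) is zero by rule in the intervention arm and (b) is zero by rule in the control arm. Do not make their unweighted sum the headline, and do not interpret (a) alone as evidence of benefit. Enter both errors in the Markov model of section 6.3.

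Cost: wording in two places and a small number of extra genotypes. If 20-60% of 51 intervention-arm failures had no detectable drug level (assumption), that is 51 x 0.20 = 10 to 51 x 0.60 = 31 samples. Table 4 already provides for DBS storage at these visits, and genotyping of stored DBS is already planned. The downside is a less favourable headline for the strategy.

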### 5.1.3 Intervention arm follow-up – Intensified HIV treatment monitoring

300 patients randomly assigned to this arm will be monitored using the investigational intensified monitoring strategy. This strategy consists of 3-monthly VL monitoring at month 9, 12, 15, 18, 21 and 24 (after start of ART in initiating patients or after the last VL measurement in patients on ART). If a VL measurement > 1000 copies/mL is detected, the patient will be called back for a follow-up study visit at the next monthly medication collection visit (4 weeks after detection of elevated VL). Upon arrival DLM is performed, the VL measurement is repeated, and a DBS prepared and stored at room temperature. Procedures following this depend on the result of DLM:

- If drug levels are detected by DLM, the result of the VL measurement is awaited. If the repeat VL is >1000 copies/ml, the DBS is shipped directly by courier to the WHO reference laboratory for drug resistance testing. The reference laboratory will provide feedback by means of a digital resistance report to the coordinating research physician. The patient will be called back for a second follow-up study visit at the next monthly medication visit (8 weeks after detection of elevated VL), either for prescription of second-line therapy or continuation of first-line therapy, guided by the

result of resistance testing.

- If DLM at the first follow-up visit indicates that drug levels are not detected, intensified counselling is performed at the same visit and first-line therapy will be maintained, regardless of the result of the repeat VL measurement. The patient will not be called back and the next VL will be performed at the next scheduled three-monthly time point. However, if the VL result at this visit is again >1000 copies/ml, drug resistance testing will be performed regardless of the outcome of DLM.

For a full overview of study visits and clinical algorithms in the control arm, see Figure 1: ITREMA study flowchart.

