### 6.3 Cost-effectiveness of intensified monitoring

The cost increases associated with the intensified monitoring strategy will be compared with the (estimated) cost reductions by prevention of unnecessary switches to a more costly regimen and differences in other study outcomes between arms. To evaluate the cost-effectiveness of the intensified monitoring strategy we will assess the effects of the intensified monitoring strategy on reduction of resistance accumulation and unnecessary treatment switches in a model-based approach with several levels of detail. The first assessment will concern the net cost of implementing tailored patient management based on DBS for resistance genotyping. A Markov model will be developed to estimate the costs over a fixed time period following initiation of ART. Secondly, we will assess the cost-effectiveness of implementing decentralized drug level testing. Here, we will extend the Markov model with known evidence on health outcomes in South Africa, i.e. quality of life using a standardized item scale and mortality. With the extended model the costs and effects, in terms of life-years and quality-adjusted life-years (QALYs) gained, as well as the incremental costs and ICER of (different components of) the intensified monitoring strategy will be estimated. Finally, we will analyze cost-effectiveness from the societal perspective and take indirect costs and benefits into account, e.g. costs and benefits that are generated by the impact of treatment on patients' productivity and participation in society. To fully take indirect effects into account dynamic transmission modeling is necessary. Sensitivity analyses will be performed in order to ascertain how the (cost)-effectiveness of various monitoring schemes depends on behavioral parameters, on treatment uptake and adherence, and other key model parameters.

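### The definition of an averted unnecessary switch is not tied to the control arm's switch rule, so it counts intervention patients whom standard care would not have switched

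*Protocol*

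**What the plan says.** Section 3.1 makes prevention of unnecessary treatment switches part (2) of the primary objective. Section 6.1 measures it with two counts. For the intervention arm: "An averted case of unnecessary switching will be defined as two sequential elevated VL results in the intervention arm without presence of resistance mutations". For the control arm, unnecessary switches actually made are to be found by retrospective genotyping.

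The arms reach two elevated VLs by different routes:

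- **Control (5.1.2).** "Viral load measurements will be performed at month 12 and 24 after start of ART"; for patients already on ART, the same months counted from their last VL. An elevated result leads to counselling and a "repeat VL measurement, 2 months after the initial VL measurement". The switch rule rests on that second result: "If the repeat VL measurement is >1000 copies/ml after adherence counselling, this is taken to be indicative of therapy failure", and the patient is switched.
- **Intervention (5.1.3).** "3-monthly VL monitoring at month 9, 12, 15, 18, 21 and 24". An elevated result leads to a call-back "4 weeks after detection of elevated VL", where the VL is repeated on arrival.

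On genotyping in the intervention arm, section 5.2.4.1 says: "In case DLM detected no drug level, the DBS is not sent and genotyping not performed". Section 6.3 lists "cost reductions by prevention of unnecessary switches to a more costly regimen" among the offsets in the cost analysis.

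**The concern.** An averted event is a counterfactual: it needs a patient whom the comparator strategy would have switched. The section 6.1 definition never asks for that. It takes the intervention arm's own detection scheme, which has three times as many scheduled tests and half the confirmation interval, and credits every mutation-free pair as a switch prevented. A non-resistant episode that starts after month 12 and clears before month 24 can be scored as averted, although a control patient with the same episode would have had no scheduled VL during it.

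The two halves of the outcome also differ in kind. One is a hypothetical count in one arm and the other an observed count in the other arm, so setting them side by side does not use the randomisation. At stake is the measure for one of three parts of the primary objective, and possibly a cost offset.

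**Working it through.** The protocol states no expected number, rate or power for averted switches, so there is no figure of its own to reproduce. The check applies both rules to the same non-resistant viraemic episodes.

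**Inputs from the protocol.** Intervention tests at months 9, 12, 15, 18, 21 and 24, repeated 1 month later (5.1.3; a protocol month is 28 days). Control tests at months 12 and 24, repeated 2 months later (5.1.2).

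**Assumptions not in the protocol.** One episode per patient, with onset uniform over months 6 to 24 and exponential duration with mean m months. Call-backs after month 24 take place. There is no counselling effect and no unscheduled testing.

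**Formulas.** An episode meets a rule if it is still present at the repeat following the first scheduled test after onset. Integrating over onset:

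- Intervention: P_I = (6/18) · m · e^(−1/m) · (1 − e^(−3/m))
- Control: P_C = (1/18) · m · e^(−2/m) · (2 − e^(−6/m) − e^(−12/m))
- Ratio: P_I/P_C = e^(1/m) × 6(1 − e^(−3/m)) / (2 − e^(−6/m) − e^(−12/m))

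The factor e^(1/m) comes from the shorter confirmation interval. The rest comes from six rather than two test occasions. Every episode that meets the control rule also meets the intervention rule, so the share of averted cases that standard care would not have switched is 1 − P_C/P_I.

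| Mean duration (months) | P_I | P_C | Ratio | Ratio from test frequency alone | Share not meeting control rule |
|---|---|---|---|---|---|
| 1 | 0.117 | 0.015 | 7.8 | 2.9 | 87% |
| 2 | 0.314 | 0.080 | 3.9 | 2.4 | 75% |
| 3 | 0.453 | 0.158 | 2.9 | 2.1 | 65% |
| 6 | 0.666 | 0.357 | 1.9 | 1.6 | 46% |
| 12 | 0.814 | 0.579 | 1.4 | 1.3 | 29% |
| 24 | 0.902 | 0.754 | 1.2 | 1.15 | 16% |

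Simulation of the same model agrees to within sampling error (7.7 to 7.9 at 1 month, 1.2 at 24 months). The ratio exceeds 1 throughout.

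**Scale.** With 300 patients per arm, 20% failure and 10% loss per year over 1.5 years (5.1.3, 6.7.3), 300 × 0.20 × 0.85 = 51 failures per arm. Section 2.1 cites 13–35% of failures without resistance under six-monthly or yearly VL monitoring: 51 × 0.13 = 6.6 to 51 × 0.35 = 17.9, so about 7 to 18 patients. At these numbers a few misclassified cases matter.

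**Genotype status.** The definition requires absence of mutations. Patients with two elevated VLs and no detectable drug level are not genotyped at that point (5.2.4.1). They are genotyped if the next three-monthly VL is again elevated (5.1.3, 5.2.4.1). The sample list in 5.1.3, placed under the intervention arm although its text names the control arm, provides for retrospective testing of stored dried blood spots (DBS) in clinical therapy failure. Section 5.2.6 provides for it in the control group only. Whether a patient who resuppresses after the second elevated VL ever receives a genotype is therefore unclear.

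**The case against.** Several points on the other side are fair.

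- **Another between-arm outcome exists.** A reader might infer that objective (2) has no valid comparison at all. That goes too far. Section 6.1 also lists the rate of virological failure without resistance in both arms, and control-arm unnecessary switches are ascertained by genotyping. Nor does section 6.1 say that averted and made switches are to be subtracted. Section 6.1 does claim equal measurement frequency through retrospective testing, but 5.1.2 limits retrospective control VLs to clinical therapy failure, so control episodes that clear between tests remain unseen.
- **Missing genotypes need not inflate the count.** It is tempting to say that many patients are not genotyped and that this overstates the result. The protocol gives no size for that group. The count rises only if ungenotyped patients are taken as mutation-free; if they are left out, it falls. The direction is unknown.
- **The cost link is not stated.** A reader might infer that the count goes straight into the Markov model. Section 6.3 describes a model-based estimate and does not name this count as an input.
- **Counselling before the repeat.** Section 5.1.2 places the control repeat after adherence counselling, but 5.2.4.2 can be read as placing both at one visit. The calculation therefore assumes no counselling effect. An effect before the control repeat would widen the gap.
- **Unscheduled control tests.** Section 5.2.3 allows VL testing outside the schedule when clinical abnormalities are found. This would narrow the gap somewhat, but such tests are prompted by symptoms rather than made routinely.
- **The proposed contrast is close to a planned count.** The intervention arm is to switch only when resistance is detected (2.2), so its proportion should be near zero. That is an effect of the strategy, and a comparison by randomised arm measures it properly.

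None of this ties the definition to the control rule.

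**Conclusion.** The definition is wrong as written. It is met by intervention patients whom standard care would not have switched, so as a count of switches averted it is biased upward, and paired with the observed control-arm count it is not a randomised comparison.

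The direction follows from the two schedules. The size does not: it runs from about 1.2 times (mean duration 24 months) to about 8 times (1 month), under the assumptions listed above. No single figure, such as a doubling, should be quoted, because the protocol gives neither the duration of viraemia nor the time to mutation. If the count is used for the cost offset in section 6.3, the saving would be overstated; the protocol does not say that it will be. The status of some ungenotyped patients under the definition is uncertain, with unknown direction of error.

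**What to change.** 1. For objective (2), define one outcome in section 6.1: the proportion of all randomised patients switched to second-line therapy by the end of follow-up, including call-backs, with no relevant resistance mutation on the DBS taken at the switch decision. Report the risk difference between arms with its 95% confidence interval.
2. Use this contrast for any switch-related input to the cost analysis in section 6.3.
3. Keep averted cases as description only, or restrict them to cases that also meet the control rule's timing (elevated at month 12 or 24 and again two months later). The four-week repeat alone cannot show the latter, so the restricted count would need a VL at that time, for example from stored plasma where a sample exists.
4. Reconcile sections 5.1.3 and 5.2.6 on which patients have stored DBS tested retrospectively, and state how a patient without a genotype is classified.

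The cost is mainly outcome wording. Genotyping of control failures (5.2.6) and before intervention-arm switches (5.2.4.1) is already planned, DBS are stored at call-back visits (Table 4), and no patient's management changes. Extra laboratory work arises only if the averted count is kept and the remaining stored samples are tested for it.
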